**Figure 2 F2:**
[figure not shown]
Time schedule of enrollment, interventions, and assessments: In the run-in period, Subjects will receive health education on constipation by specialist personnel and inform consent, General patient information will be collected; At baseline (week 0) and at 4, 8, 16 wk, CSI will be used to assess the severity of constipation; the PAC-QOL questionnaire to evaluate the impact of constipation on the quality of life of patients with PD; and BSFS to assess stool characteristics. The MDS-UPDRS scale will be used to comprehensively evaluate patients’ daily life experience including MS, NMS, and motor complications. The NMSS allows quantitative evaluation of NMS of PD; the PDSS is used to assess sleep quality in PD patients; and PFS-16 measures the severity of fatigue; the Physiologic information and Safety indices will also be tested at baseline (week 0) and at 4, 16 wk; adverse events will be recorded during the research. BSFS = bristol stool form scale, CSI = constipation severity instrument, MDS-UPDRS = the new world movement disorders comprehensive Parkinson disease rating scale, NMS = nonmotor symptoms, NMSS = nonmotor symptoms scale, PAC-QOL = patient assessment of constipation quality of life questionnaire, PDSS = Parkinson disease sleep scale, PFS-16 = Parkinson fatigue scale.

We will collect a range of demographic information, including name, sex, age, date of birth, height, weight, education, history of tobacco and alcohol use, family history of PD, occupation, home address, and contact telephone number. We will also record each patient's medical history, including current medical status and past medical history. Physiological data will include pulse, respiration, heart rate, standing blood pressure, and nervous system function. Safety indicators will include routine blood, urine, and stool parameters; liver and kidney function; and electrocardiography parameters. Any adverse events after the start of treatment will be recorded along with incident handling.

## Quality control

13

Before the start of the study, the investigators will receive standardized training relating to the data collection strategy and guidelines for the different scales that will be used to assess outcomes. During the trial, data will be collected by trained researchers to prevent bias. If the subjects experience the “on-off” phenomenon (In Parkinson patients, the alternating periods of good control (on) and poor control (off) of their symptoms. The on-off phenomenon is often experienced in patients undergoing L-dopa therapy), the visit should be conducted during the “on” period.

## Data management

14

An electronic data capture (EDC) system, that relies on the clinical research data platform of the Parkinson Medical Center at the Beijing Rehabilitation Hospital, will be used for all data entry and management. Data entry will be carried out by 1 data collector assigned to each center. Participant information will be stored in the EDC system; investigators will access this system using a password. The investigators will also check the case report forms to confirm that they are complete and also check for consistency between the code and the subject's screening entry list. Data will be validated after entry into the EDC system, and the original case will be reviewed again based on these results. Final data will be exported as an Excel (Microsoft, Redmond, WA) spreadsheet.

## Data monitoring

15

We have already established an independent Data and Safety Monitoring Board (DSMB) for this study that is independent of the sponsor, consisting of a TCM specialist, a Neurologist and a statistician. The DSMB will oversee whether the trial follows the study design and standard guidelines. The neurologist will assess, manage, and classify all adverse events. All serious adverse events will need to be reported to the main researchers, the Ethics Committees, and the DSMB, within 24 hours of occurrence. The DSMB and the main researchers will discuss such issues. The Ethics Committees and the DSMB will have the right to terminate the trial if they deem that such action is appropriate. The role of the statistician is to review the safety data.

## Statistical analysis

16

SPSS v20.0 software (SPSS Inc., Chicago, IL) will be used for all data processing and analysis. Measurement data will be expressed as mean ± standard deviation. The normality and homogeneity of variance will be tested. Data with a normal distribution and uniform variance will be evaluated with the independent samples *t*-test for between-group comparisons. Data that do not meet these criteria will be evaluated with a nonparametric test. Repeated measures analysis of variance will be used for within-group comparisons (1-way analysis of variance will be used if the data meet the Huynh–Feldt condition; otherwise, a mixed model will be used).

Numerical (count) data will be expressed as percentages. Between-group comparisons will be performed with the *χ*^2^ test. Intent-to-treat and compliance analyses will be performed to compare efficacy between the 2 groups. The last observation carry-forward method will be used for data processing. The significance level for each test will be set at *P* < .05.

An intention-to-treat analysis will be adopted to deal with missing data, including all participants in the analysis based on the initial group allocation. A linear mixed model approach (a direct likelihood estimation method) will be applied to analyze all continuous variables as value is missing at random.

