## Sample size

7

The minimum sample size for statistical significance with a 2-sample 1-sided *t* test was estimated based on the results of a previous study involving the treatment of patients with PD-related constipation.^[13]^ Based on a 2:1 ratio of patients in the BYZJ and placebo groups, the minimum sample size was calculated with formula shown in Eq. (1).: 

In Equation 1, n represents the sample size of each group, κ = nA/nB; μ represents the overall mean, μA represents the mean of group A, μB represents the mean of group B; σ represents the overall standard deviation, σA represents the standard deviation of group A, σB represents the standard deviation of group B; α represents type 1 errors; and β represents type 2 errors. Application of Eq. (1) showed that 52 are required for the BYZJ group and 26 cases are required for the placebo group. Considering a 15% dropout rate, we plan to recruit 60 and 30 cases for the BYZJ and placebo groups, respectively.

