## Outcome measures and safety

12

We will collect a range of general information for each patient during the run-in period. The primary and secondary outcomes will be assessed at week 0 (baseline), and then again at weeks 4, 8, and 16. Safety and laboratory indicators will be assessed at week 0 (baseline), and then again at weeks 4 and 16 (Fig. 2). The primary outcome will be the change in constipation severity instrument score. Secondary outcomes include scores for the Patient Assessment of Constipation Quality of Life questionnaire, the Bristol stool form scale, the movement disorders-unified Parkinson disease rating scale, the nonmotor symptoms scale, the Parkinson disease sleep scale, and the Parkinson fatigue scale. We will also record the dose of laxatives and their frequency of use.

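### Section 16 gives two incompatible rules for the same repeated scores: a Huynh–Feldt switch for within-group change, and a linear mixed model for all continuous variables

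*Protocol article*

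**What the plan says.** All statements are in the protocol article.

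- Section 12 (Outcome measures and safety) sets four measurement times per patient: "The primary and secondary outcomes will be assessed at week 0 (baseline), and then again at weeks 4, 8, and 16".
- Section 16 (Statistical analysis), first paragraph, gives the method for change within an arm: "Repeated measures analysis of variance will be used for within-group comparisons". A bracket in the same sentence qualifies it: "1-way analysis of variance will be used if the data meet the Huynh–Feldt condition; otherwise, a mixed model will be used".
- Section 16, last paragraph, gives another rule: "A linear mixed model approach (a direct likelihood estimation method) will be applied to analyze all continuous variables as value is missing at random".
- Section 16 also states "The last observation carry-forward method will be used for data processing", and a threshold of .05 for every test.
- Section 7 (Sample size) gives the arm sizes: "52 are required for the BYZJ group and 26 cases are required for the placebo group", raised to 60 and 30 for dropout.

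**The concern.** The scale scores at weeks 0 to 16 are continuous variables, so they fall under both rules. If every continuous variable goes to a linear mixed model, the ANOVA branch of the bracket is never used. If the bracket governs, the last paragraph is not true of within-group change. An analyst cannot follow both.

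The bracket has two further weaknesses:

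- **Wording.** Taken alone, the name of the test in the bracket denotes the independent-groups ANOVA. The four visits come from the same patients, so that test would leave the between-patient variance in the error term.
- **Data-driven choice.** Even if the repeated-measures version is meant, the method depends on the outcome of a sphericity check. Nothing says whether the check is made once for both arms or separately in each. If separately, BYZJ and placebo can be analysed by different methods on the same scale. The check also has unequal power in arms of 60 and 30.

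At stake are the within-arm P values and any sentence that sets one arm's change beside the other's.

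**Working it through.** **The two rules side by side**

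| | First paragraph, bracket | Last paragraph |
|---|---|---|
| Data | Within-group change in measurement data | All continuous variables |
| Method | 1-way ANOVA or mixed model | Linear mixed model |
| Chosen by | Huynh–Feldt condition | Fixed in advance |

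They agree only when the condition fails.

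**Inputs from the document.** Four visits; nominal level .05; arms of 60 and 30. The arm sizes follow from 52 × 1.15 = 59.8 and 26 × 1.15 = 29.9. No other figure in the plan bears on this point.

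**Inputs assumed.** The document gives no correlations, standard deviations or changes over time. I took normal, complete data with equal SDs and two covariance families: compound symmetry (sphericity true), and correlation decaying with time (AR type, stated per 4 weeks). There were 20,000 simulated data sets per case.

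**Step 1: the literal reading.** With k = 4 visits and n patients:

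- Independent groups: F = [SS(visit)/3] / [(SS(total) − SS(visit)) / (4(n − 1))]
- Repeated measures: F = [SS(visit)/3] / [(SS(total) − SS(visit) − SS(patient)) / (3(n − 1))]

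Under compound symmetry with no change over time, the visit mean square has expectation σ²(1 − ρ). The independent-groups error mean square has expectation σ². The F ratio is therefore shrunk by about 1 − ρ, which makes the test too conservative.

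| ρ | Type I error, independent groups (n = 60 / 30) | Type I error, repeated measures (n = 60 / 30) |
|---|---|---|
| 0.3 | 0.011 / 0.011 | 0.049 / 0.049 |
| 0.5 | 0.002 / 0.002 | 0.050 / 0.048 |
| 0.7 | 0.0000 / 0.0001 | 0.050 / 0.051 |

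For assumed falls of 0.4, 0.3 and 0.2 SD at weeks 4, 8 and 16 with ρ = 0.5, power is 33% against 77% at n = 60, and 10% against 44% at n = 30 (independent groups against repeated measures).

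**Step 2: the repeated-measures reading, with the check made in each arm.** Let a and b be the probabilities that Mauchly's test at .05 rejects in the larger and smaller arm. The arms get different methods with probability a(1 − b) + b(1 − a).

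- Sphericity true: 2 × 0.05 × 0.95 = 0.095. The simulation gives 0.092 to 0.098.
- AR 0.3: 0.320 × 0.839 + 0.161 × 0.680 = 0.38.
- AR 0.5: 0.801 × 0.572 + 0.428 × 0.199 = 0.54.
- AR 0.7: 0.988 × 0.217 + 0.783 × 0.012 = 0.22.
- AR 0.8: 0.998 × 0.103 + 0.897 × 0.002 = 0.10.

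So the range is roughly 9% to 55%. When sphericity is false, the smaller arm keeps the ANOVA more often only because the check has less power there.

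**Step 3: does the switch distort the error rate?** Repeated-measures ANOVA used throughout has type I error of 0.048 to 0.052 under compound symmetry and 0.050 to 0.064 under AR. The two-step rule stays near 5% to 6%. The highest value found is about 6.8%, in the smaller arm at n = 26.

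**Step 4: does it distort the contrast between arms?** I counted data sets in which BYZJ is significant and placebo is not, with n = 51 and 25 and 6,000 runs. An unstructured multivariate test stands in for the mixed model.

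| Assumed pattern | Switch | One method in both arms |
|---|---|---|
| No change; AR 0.7, SDs 1/1.4/1.3/1.2 | 5.3% | 5.1% |
| Same fall in both arms; same covariance | 42.0% | 42.2% |
| Same fall; equal SDs | 44.5% | 43.8% |
| Same fall; compound symmetry 0.6 | 43.2% | 45.4% |

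In the first pattern the methods differed between arms in about 51% of data sets, yet the contrast rate hardly moved.

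**The case against.** A reader might infer from the bracket that the plan treats the four visits as independent. The document does not support that. The bracket sits inside a sentence that names repeated-measures ANOVA, and the Huynh–Feldt condition describes the covariance of repeated measurements within a patient. It has no role in an independent-groups test. The natural meaning is a one-factor repeated-measures ANOVA, so Step 1 shows only what careless execution would cost. Even then the test would be conservative and would not create false positives.

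A reader might also infer that the check is made separately in each arm. The text says only that the data must meet the condition. A per-arm check is plausible because the comparisons are within group, but a pooled check is possible, and a condensed article may leave that to the full analysis plan.

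Finally, it is tempting to say that unlike methods would manufacture an apparent difference between arms. Step 4 does not bear this out. The high rate of one arm being significant and the other not comes from unequal arm sizes and from within-arm testing itself, and a single method would leave it essentially unchanged.

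These objections stand, and they limit the point. They do not remove the contradiction. Both rules are printed in the same section for the same data, so this is not a detail left to another document. The mixed model for all continuous variables also sits awkwardly with the t-test planned between groups, but that wider conflict does not settle which rule applies to within-group change.

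**Conclusion.** The point holds as a minor inconsistency. Section 16 states two rules for the same repeated scores that cannot both be followed. One of them uses loose wording and lets a sphericity check choose the test.

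- **If the bracket is run literally:** type I error far below 5% (about 0.002 at a correlation of 0.5) and a large loss of power. This is the less likely reading.
- **On the likelier reading, with a check in each arm:** different methods by arm in roughly 9% to 55% of trials, error rates of about 5% to 7%, and little effect on contrasts between the arms' within-group results.
- **Between-group comparison:** specified separately and not touched by the switch.

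Every correlation, SD and effect size above is an assumption. The simulations use complete normal data, so they do not show what happens if one branch uses carried-forward values and the other uses observed data only.

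**What to change.** Delete the bracket with the Huynh–Feldt condition. State that change within each arm will be estimated from the single linear mixed model already named in the last paragraph of section 16. That model contains both arms, with visit as a category, arm, arm-by-visit, unstructured within-patient covariance and no sphericity pre-test. Each arm's change from week 0 is then a contrast from one fitted model.

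The cost is one sentence of analysis wording. No patients, visits or data are added. The change removes the contradiction, the ambiguous test name and the possibility of different methods by arm.

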**Methods and analysis::**

This randomized, double-blind, placebo-controlled, multicenter clinical trial will involve 4 hospitals in Beijing, China. The study will aim to recruit 90 PD patients with constipation between 30 and 80 years-of age with a score of 1 – 4 on the Hoehn and Yahr scale. Once recruited, Patients will be randomized into a BYZJ group or a placebo group in a 2:1 ratio. The trial will include a 1-week run-in period, a 4-week double-blind treatment period, a 4-week and a 12-week follow-up period. All patients will be educated about PD-related constipation during the run-in period. BYZJ granules and simulated granules will be administered twice daily for 4 weeks to the BYZJ group and the placebo group respectively. Assessments will be performed during run-in period, before the start of treatment (baseline, week 0), and at 4, 8, and 16 weeks. The primary outcome will be measured with the Constipation Severity Instrument, and secondary outcomes will be evaluated with the Patient Assessment of Constipation Quality of Life questionnaire, Bristol Stool Form Scale, Movement Disorders–Unified Parkinson Disease Rating Scale, Nonmotor Symptoms Scale, PD Sleep Scale, Parkinson Fatigue Scale-16. Laxative use (dose and frequency) will also be recorded. Intention-to-treat and per-protocol set analyses will be used to compare symptom improvement between the 2 groups. Any adverse events will be recorded.

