## Study design

4

This will be a randomized, double-blind, and placebo-controlled multicenter trial. We aim to recruit 90 patients who will be assigned by stratified randomization (in a 2:1 ratio) to intervention (BYZJ) and control (placebo) groups. The total study duration will be 9 weeks, with a 1-week run-in period, an intervention time of 4 weeks, and 4-week and 12-week washout follow-up periods. Efficacy and safety will be assessed at baseline (week 0) and at 4, 8, and 16 weeks (Fig. 1).

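### The Statistical analysis section prescribes both LOCF and a direct-likelihood mixed model for the same continuous outcomes without saying which is primary, and LOCF suits this design badly

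*Protocol article*

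**What the plan says.** Section 16, Statistical analysis, makes four statements that bear on the analysis of a continuous outcome with missing values:

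- First paragraph: "Data with a normal distribution and uniform variance will be evaluated with the independent samples *t*-test for between-group comparisons". Data that fail these conditions go to a nonparametric test. A mixed model appears here only as a fallback for within-group comparisons.
- Second paragraph, after the rule for count data: "Intent-to-treat and compliance analyses will be performed to compare efficacy between the 2 groups". The next sentence is "The last observation carry-forward method will be used for data processing".
- Third paragraph: "An intention-to-treat analysis will be adopted to deal with missing data, including all participants in the analysis based on the initial group allocation".
- Third paragraph, next sentence: "A linear mixed model approach (a direct likelihood estimation method) will be applied to analyze all continuous variables as value is missing at random".

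No method is called primary or sensitivity. Neither missing-data method is tied to an analysis set, and LOCF is not tied to a type of variable or to a visit.

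On the design, the Abstract gives 4 weeks of treatment: "BYZJ granules and simulated granules will be administered twice daily for 4 weeks to the BYZJ group and the placebo group respectively". Section 4, Study design, places the later visits off treatment: "an intervention time of 4 weeks, and 4-week and 12-week washout follow-up periods". Section 12, Outcome measures and safety, makes the change in CSI score the primary outcome, measured at weeks 0, 4, 8 and 16, and names no primary visit. Section 7, Sample size, allows for 15% dropout.

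**The concern.** LOCF and direct likelihood are alternative answers to the same question. LOCF fills each gap on the assumption that the score stays constant after the last visit. Direct likelihood uses the observed values as they are and assumes missing at random. Applied to the same outcome they can give different estimates. The t-test rule adds a third candidate for the between-group comparison. An analyst could follow any of these sentences and claim to have followed the plan, and the choice could be made after the results are seen.

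The visit schedule makes LOCF a poor choice in its own right. Week 4 is the first visit after baseline and the last on treatment, so every value carried into week 4 is a baseline value. A value carried from week 4 into weeks 8 or 16 is an end-of-treatment score standing in for an off-treatment one, at the visits that would show whether an effect lasts.

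**Working it through.** **1. The plan's own figure.** Dropout of 15% is the only stated number that bears on missing data. 52 × 1.15 = 59.8 and 26 × 1.15 = 29.9, which reproduces the planned 60 and 30. At that rate 0.15 × 60 = 9 BYZJ patients and 0.15 × 30 = 4.5 placebo patients would lack later scores.

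**2. Does the same outcome fall under both methods?** CSI change is continuous, so the mixed-model sentence covers it. It is an efficacy outcome, and the LOCF sentence directly follows the one on intention-to-treat and compliance efficacy analyses, with no restriction. It also falls under the t-test rule. No ranking is given.

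**3. What LOCF enters, by time of loss**

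| Last visit seen | Week 4 | Week 8 | Week 16 |
|---|---|---|---|
| Baseline | baseline (zero change) | baseline | baseline |
| Week 4 | observed | end-of-treatment score | end-of-treatment score |
| Week 8 | observed | observed | off-treatment week 8 score |

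Only the middle row carries an end-of-treatment score into the washout visits.

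**4. Illustration.** The documents give no effect sizes, time course or dropout timing, so these are assumptions. Mean changes in SD units: week 4, BYZJ −1.0 and placebo −0.4 (difference 0.60); week 16, both −0.2 (difference zero). Loss is at random within each arm.

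For loss between weeks 4 and 8 at rate d, the LOCF mean at week 16 in each arm is (1 − d) × week 16 mean + d × week 4 mean.

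| Loss BYZJ / placebo | BYZJ | Placebo | Spurious difference |
|---|---|---|---|
| 15% / 15% | 0.85(−0.2) + 0.15(−1.0) = −0.32 | 0.85(−0.2) + 0.15(−0.4) = −0.23 | −0.09 |
| 20% / 10% | 0.80(−0.2) + 0.20(−1.0) = −0.36 | 0.90(−0.2) + 0.10(−0.4) = −0.22 | −0.14 |
| 10% / 20% | 0.90(−0.2) + 0.10(−1.0) = −0.28 | 0.80(−0.2) + 0.20(−0.4) = −0.24 | −0.04 |

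If instead all 15% are lost before week 4, the week 4 difference becomes 0.85 × 0.60 = 0.51.

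**5. Other assumed effects.** With differences of 0.50, 0.25 and 0 SD at weeks 4, 8 and 16 and 15% random loss per arm, a simulation gave these LOCF differences:

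- All loss between weeks 4 and 8: 0.07 at week 16.
- All loss between weeks 8 and 16: 0.04 at week 16.
- All loss before week 4: 0.43 at week 4.

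A correctly specified mixed model has none of this bias under random loss.

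**6. Scale.** With 60 and 30 patients and SD 1, the standard error of a difference is √(1/60 + 1/30) = 0.22. A bias of 0.09 is about 0.4 standard errors. It would take a nominal two-sided 5% error at week 16 to roughly 7%, and a bias of 0.14 to roughly 10%, ignoring any effect of LOCF on the variance.

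**The case against.** The strongest reply is that the two sentences can be read together. The mixed-model sentence states its scope, while the LOCF sentence has none and sits in a paragraph that opens with count data. LOCF might then be meant for categorical data, or as a second analysis. The article says neither, and the sentence just before LOCF concerns efficacy comparisons in both analysis sets. What stands is that nothing in the text says LOCF comes first and the mixed model is then fitted to the filled data. A reader might infer that sequence, but the documents do not support it. The fault is two unranked methods.

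A reader might also infer that LOCF would put a false lasting effect into the primary result. The documents do not support that either. No primary visit is named. If it is week 4, no on-treatment score can be carried into it, and in the illustration LOCF weakens the effect. The carry-over into both washout visits concerns only patients last seen at week 4.

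It is fair, too, that the sizes are assumed and modest, and that the week 4 and week 16 biases cannot both occur at full size because each uses the whole 15%. LOCF treats filled values as observed, so understated standard errors are a risk, but that was not quantified and is not claimed here.

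Finally, the article may leave detail to an analysis plan that is not shown. That excuses an omission. It does not excuse stating methods that compete for the same outcome.

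**Conclusion.** The point holds as a conflict within section 16. CSI change and the other continuous scales fall under LOCF, a direct-likelihood mixed model and a t-test or nonparametric rule, with no order among them. This rests on the text alone.

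That LOCF suits the design badly follows from the visit schedule. Its numerical effect is illustrative: a false week 16 difference of about 0.09 SD (0.04 to 0.14 across the unequal-loss patterns), or a week 4 difference cut from 0.60 to 0.51 SD. Direction and size depend on the true time course and on when, and in which arm, patients leave, none of which the documents give.

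**What to change.** Before unblinding, amend section 16 to do three things:

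1. Make the linear mixed model, fitted to observed data without prior imputation, the primary between-group analysis for CSI and the other continuous scales. Include baseline score, treatment, visit and treatment-by-visit, and take the contrast at a primary visit named in advance.
2. State that this model replaces the t-test or nonparametric rule for between-group comparison of those outcomes. Removing LOCF alone would leave that conflict in the text.
3. Delete the LOCF sentence, or label LOCF as a sensitivity analysis only. Either removes the contradiction.

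Covariance structure, a centre effect and the choice of sensitivity analysis for data missing not at random can be left to the statistical analysis plan.

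The cost is a wording change in the protocol, matched in the analysis plan if one exists. The mixed model is already planned, and no visits, patients or data are added.
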